### RQ4 analyses: Moderating effects

RQ4 hypotheses concern moderating effects, that is, hypotheses regarding whether the strength of an observed intervention effect on an outcome variable depends on another variable. In other words, RQ4 hypotheses involve hypotheses regarding interaction effects between interventions and other variables. These hypotheses are also tested with mixed effects modelling.

Firstly, we hypothesize that both the SEMLA and DIL intervention effects on selective attention, EF score, Language score and TEC will be negatively moderated by SES. That is, the intervention effects should be stronger on low-SES children than they are on high-SES children. These negative SES moderation hypotheses are tested with the model

$$ {\mathrm{POSTSCORE}}_{\mathrm{ijk}}=\kern0.5em {\upalpha}_{0\mathrm{jk}}+{\upalpha}_{00\mathrm{k}}+{\upbeta}_1{{\mathrm{INTERVENTION}}_{0\mathrm{jk}}}^{\ast }\ {\upbeta}_2{\mathrm{SES}}_{\mathrm{ijk}}+{\upbeta}_3{\mathrm{PRESCORE}}_{\mathrm{ijk}}+{\upvarepsilon}_{\mathrm{ijk},}\ {\upvarepsilon}_{\mathrm{ijk}}\sim \mathrm{N}\left(0,{\upsigma^2}_{\upvarepsilon \mathrm{ijk}}\right),{\upalpha}_{\mathrm{j}}\sim \mathrm{N}\left(0,{\upsigma^2}_{\upalpha \mathrm{j}}\right),{\upalpha}_{\mathrm{k}}\sim \mathrm{N}\left(0,{\upsigma^2}_{\upalpha \mathrm{k}}\right) $$

These models predict the postscore for child *i* as a function of the interaction between the intervention at preschool unit *j* and the SES score for child *i* while controlling for the prescore measure of child *i*, centered around zero. They also include individual intercepts α for each preschool *k* and for each preschool unit *j*, thereby controlling for differences between preschool units and preschools.

Secondly, both the SEMLA and DIL intervention effects on EF are hypothesized to be negatively moderated by the EF score at pretesting. In other words, the intervention effects on EF should be stronger on low-EF children than on high-EF children. This negative EF moderation hypothesis is tested with the model

$$ \mathrm{EF}\_{\mathrm{POSTSCORE}}_{\mathrm{ijk}}=\kern0.5em {\upalpha}_{0\mathrm{jk}}+{\upalpha}_{00\mathrm{k}}+{\upbeta}_1{{\mathrm{INTERVENTION}}_{0\mathrm{jk}}}^{\ast }\ {\upbeta}_2\mathrm{EF}\_{\mathrm{PRESCORE}}_{\mathrm{ijk}}+{\upvarepsilon}_{\mathrm{ijk},}\ {\upvarepsilon}_{\mathrm{ijk}}\sim \mathrm{N}\left(0,{\upsigma^2}_{\upvarepsilon \mathrm{ijk}}\right),{\upalpha}_{\mathrm{j}}\sim \mathrm{N}\left(0,{\upsigma^2}_{\upalpha \mathrm{j}}\right),{\upalpha}_{\mathrm{k}}\sim \mathrm{N}\left(0,{\upsigma^2}_{\upalpha \mathrm{k}}\right) $$

in which the EF postscore for child *i* is predicted on the basis of the interaction between the intervention at preschool unit *j* and the EF prescore of child *i*. It also includes individual intercepts α for each preschool *k* and each preschool unit *j*.

Thirdly, the SEMLA intervention effects on selective attention, EF score, math, TEC, communication score and the language score are expected to be positively moderated by the total ECERS score. In other words, there should be a stronger effect of the SEMLA intervention in high-quality preschools as estimated by the total ECERS score. These positive ECERS moderation hypotheses are tested with the model.

$$ {\mathrm{POSTSCORE}}_{\mathrm{ijk}}=\kern0.5em {\upalpha}_{0\mathrm{jk}}+{\upalpha}_{00\mathrm{k}}+{\upbeta}_1{{\mathrm{INTERVENTION}}_{0\mathrm{jk}}}^{\ast }\ {\upbeta}_2{\mathrm{ECERS}}_{00\mathrm{k}}+{\upbeta}_3{\mathrm{PRESCORE}}_{\mathrm{ijk}}+{\upvarepsilon}_{\mathrm{ijk},}\ {\upvarepsilon}_{\mathrm{ijk}}\sim \mathrm{N}\left(0,{\upsigma^2}_{\upvarepsilon \mathrm{ijk}}\right),{\upalpha}_{\mathrm{j}}\sim \mathrm{N}\left(0,{\upsigma^2}_{\upalpha \mathrm{j}}\right),{\upalpha}_{\mathrm{k}}\sim \mathrm{N}\left(0,{\upsigma^2}_{\upalpha \mathrm{k}}\right), $$

which predicts the postscore of the *i*th child from the interaction between the intervention at preschool unit *j* and the total ECERS score of preschool *k*, while controlling for the prescore of child i. Again, these models include individual intercepts α for each preschool *k* and each preschool unit *j*.

### RQ5 analyses: Background - outcome relationships

RQ5 hypotheses concern relationships between outcome variables and background variables. These will be tested with mixed effects models with the structure

$$ {\mathrm{SCORE}}_{\mathrm{ijk}}=\kern0.5em {\upalpha}_{0\mathrm{jk}}+{\upalpha}_{00\mathrm{k}}+{\upbeta}_1{\mathrm{Y}}_{\mathrm{ijk}}+{\upbeta}_2{{\mathrm{INTERVENTION}}_{0\mathrm{jk}}}^{\ast }\ {\upbeta}_3{\mathrm{TIME}}_{\mathrm{ijk}}+{\upbeta}_4{\mathrm{FIDELITY}}_{\mathrm{ijk}}+{\upbeta}_5{\mathrm{ECERS}}_{00\mathrm{k}}+{\upvarepsilon}_{\mathrm{ijk},}\ {\upvarepsilon}_{\mathrm{ijk}}\sim \mathrm{N}\left(0,{\upsigma^2}_{\upvarepsilon \mathrm{ijk}}\right),{\upalpha}_{\mathrm{j}}\sim \mathrm{N}\left(0,{\upsigma^2}_{\upalpha \mathrm{j}}\right),{\upalpha}_{\mathrm{k}}\sim \mathrm{N}\left(0,{\upsigma^2}_{\upalpha \mathrm{k}}\right), $$

predicting the outcome scores of child *i* on the basis of the background variables Y of child *i*, the interaction between the intervention at preschool unit *j* and the time of testing (pre vs. post) of child *i*, the fidelity score of child *i*, and, finally, the ECERS-3 score of preschool *k*. These models will also contain individual intercepts α for each preschool *k* and each preschool unit *j*. As these models contain parameters for the Intervention × Time interactions, they too test whether there are any significant intervention effects on the outcome scores. A positive Intervention × Time intervention effect shows that there is a positive effect on the outcome score in the given intervention group over and above any increase in the outcome score from pretesting to posttesting. Crucially, they also show which of the background variables are positively or negatively correlated with the corresponding outcome variables, even when intervention effects and differences between pre- and posttesting are controlled for.

Separate models will once again be conducted on selective attention, early maths skills, emotional comprehension, as well as on the composite measures of EF, language and communication, respectively.

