### Sample

#### Sample characteristics

The population consists of preschool children in the age range of 48 to 77 months, living in a municipality located in the eastern parts of the Stockholm metropolitan area. The sample consists of 432 children from 28 preschool units, which, in turn come from 18 preschools. Preschool units constitute clusters to which interventions are randomly assigned. Intervention assignment was constrained in the sense that units within the same preschool were always assigned either to the same intervention type or to one of the pedagogical interventions and the control group. From each preschool unit, a smaller group of children was randomly sampled (as described below) for participation in the ERP study. The size of these sub-samples was proportional to the size of the preschool unit from which they were drawn. The sample size in the ERP study is 123 individuals following attrition.

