#### Measures of communication

Communication was defined as the ability to interact in an age-adequate manner. The following behaviours were rated as either 0 (not adequate behaviour for the child’s age) or 1 (adequate behaviour for the child’s age): gaze (meeting eyes while speaking, following gaze and pointing instructions from the tester), gestures (use of complementary and/or supplementary gestures to convey or clarify verbal utterances), body posture (an at-ease appearance rather than fidgeting on the chair etc.), fluency/prosody (speaking up rather than whispering or holding objects/hands to the mouth), following instructions (cooperative versus uncooperative behaviour), turn-taking (adequate turn-taking behaviour rather than interruptions, silence, etc.), and initiative/curiosity (whether the child takes his or her own initiative in the interaction or not). The ratings were done by a rater watching 6 min of interaction from the posttest sessions, 2 min of introduction to DCCS, 2 min of story retell, and 2 min of HSKT. The rater was blind to the intervention of a specific child. The scores for the 7 behaviours were combined and divided by the maximum score of 21 ([name] & [name], Language and executive functions in Swedish preschoolers: a pilot study, submitted).

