### RQ5 analyses: Background-outcome relationships

Here, we present power analysis statistics for RQ5 analyses, concerning hypotheses regarding relationships between background variables and outcome variables. As described above, these will also be tested with mixed effects models, predicting each outcome variable as function of the background variables, the interventions and the intervention × test (pretest vs. posttest) interaction. As such, these models test the influence of each background variable on each outcome measure, as measured both at pre- and posttesting, while controlling for the influence of all other background variables as well as differences between intervention groups and intervention effects. The power analysis statistics for the background-outcome relationships are shown in Table 7. The table only shows statistics for tests of relationships that we have specific hypotheses for, including bootstrapping statistics for the beta coefficients (means and confidence intervals), *p*-values (bootstrapped p-values, mean p-values and their confidence intervals), power calculations. For tests of RQ5 hypotheses, we do not plan to conduct p-value correction; we therefore do not report p-value adjusted statistics.

**Table 7 Tab7:** Simulation statistics of analyses of background-outcome relationships between EF, on the hand, and SES, Sex, and 2nd Language, on the other, between TEC, on the one hand, and Sex and 2nd Language, on the other, and between Math and 2nd Language, and finally between Language and SES

Statistic	EFScore			TEC		Maths	Language
	SES	Sex	2nd lang.	Sex	2nd lang.	2nd lang.	SES
Mean Beta	−0.07	−0.04	−0.04	−0.20	0.02	0.02	0.02
Beta.lower	−0.16	−0.23	−0.23	−0.50	−0.25	−0.02	−0.07
Beta.upper	0.02	0.13	0.13	0.12	0.31	0.06	0.11
boot.p	.058	.327	.327	.106	.436	.145	.329
mean.p	.213	.452	.452	.295	.510	.342	.440
p.upper	.000	.012	.012	.001	.024	.001	.008
p.lower	.911	.970	.970	.948	.974	.945	.978
Power	0.38	0.09	0.09	0.26	0.05	0.21	0.10

The table shows that the power is low, or virtually non-existent, for all of the included background-outcome relationships. The strongest relationship in terms of power is that between SES and EF. However, as shown by its Beta coefficient, here the power analysis predicts a negative relationship between SES and EF, low-SES children having a somewhat better EF ability than high-SES children, opposite to the hypothesis.

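### The RQ5 mixed model enters each child's pretest and posttest score without a child-level random effect, so tests of SES, sex and language background are anti-conservative by an amount that depends on an unreported pre-post correlation

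*Protocol article*

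**What the plan says.** The Protocol article, in the statistical section 'RQ5 analyses: Background - outcome relationships', writes out the whole model. SCORE is regressed on the background variables, Intervention × Time, fidelity and ECERS. TIME is "the time of testing (pre vs. post) of child", so each child can supply two rows. The matching section under the power calculations confirms it: "these models test the influence of each background variable on each outcome measure, as measured both at pre- and posttesting".

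The stated random terms are two intercepts: "These models will also contain individual intercepts α for each preschool", and likewise for each preschool unit. Distributions are given for these two and for the residual. No term is indexed to the child across occasions.

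The same section gives the model a second use. Because it contains Intervention × Time, the article says of these models that "they too test whether there are any significant intervention effects on the outcome scores".

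RQ5 p-values are not adjusted: 'Adjusting P-values for multiple comparisons' covers RQ1 to RQ4 only, and the RQ5 power section repeats that no correction is planned. The Discussion says that the mixed models include random slopes at each level of nesting. No formula in the article contains a random slope.

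**The concern.** Two scores of one child on the same test, about eight weeks apart, can be expected to correlate after adjustment for cluster and covariates. With no child term, that correlation is left in a residual that the model assumes independent. For a covariate that does not change between occasions, the second record of a child carries less than a full record's worth of new information, yet the model counts it in full. The standard error is then too small and true null hypotheses are rejected too often.

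For a within-child contrast such as Intervention × Time the error runs the other way. Variation between children should cancel from the contrast but is charged to it.

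At stake are the RQ5 p-values for SES, sex and language background, which have no multiplicity correction to absorb the excess, and the standing of the additional intervention test. The models for RQ1 and RQ4 use the same random structure correctly, because they predict the posttest score and each child enters once. RQ2 rests on the RQ1 models.

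**Working it through.** **Inputs from the article**
- "The sample consists of 432 children from 28 preschool units, which, in turn come from 18 preschools" (Sample characteristics). At most 2 × 432 = 864 records for a behavioural outcome.
- "The sample size in the ERP study is 123 individuals following attrition" (same section). At most 2 × 123 = 246 records for selective attention.
- The communication rating comes from "watching 6 min of interaction from the posttest sessions" (Measures of communication), so it has no pretest record.
- Alpha 0.05 (Power calculations). Two-sided testing is my assumption.
- Rho is not given and is varied below.

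**The article's own figures.** Table 7 cannot be rerun without the pilot data. The size of its simulated trial reproduces: 27 clusters × 12 = 324 children. The article states no type I error for RQ5.

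**Covariates constant within child.** Let σ² be the residual variance given unit and preschool. The mean of a child's two scores has variance σ²(1+rho)/2, but the model uses σ²/2. The true standard error is therefore sqrt(1+rho) times the reported one, and

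type I error = 2 × [1 − Φ(1.96 / sqrt(1+rho))].

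| assumed rho | sqrt(1+rho) | actual size of a nominal 5% test |
|---|---|---|
| 0.2 | 1.095 | 7.4% |
| 0.3 | 1.140 | 8.6% |
| 0.5 | 1.225 | 11.0% |
| 0.7 | 1.304 | 13.3% |
| 0.8 | 1.342 | 14.4% |
| 1.0 (ceiling) | 1.414 | 16.6% |

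The size reaches 10% at rho of about 0.42 and 15% at about 0.85.

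**Simulation check.** REML fits with 432 children, 28 units, 18 preschools and assumed small unit and preschool variances; 600 runs at rho 0.3 and 700 at 0.5 and 0.7. Rejection of true nulls for SES, sex and second language:

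| rho | random terms as written | with child intercept added |
|---|---|---|
| 0.3 | 0.088, 0.085, 0.068 | 0.057, 0.050, 0.035 |
| 0.5 | 0.111, 0.124, 0.123 | 0.059, 0.053, 0.056 |
| 0.7 | 0.147, 0.144, 0.160 | 0.049, 0.057, 0.061 |

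Monte Carlo error near 13% with 700 runs is sqrt(0.13 × 0.87 / 700) = 0.013. The formula and the simulation agree to about that accuracy.

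**Intervention × Time.** A child's change has variance 2σ²(1−rho), but the model uses 2σ². The child-level standard error is too large by 1/sqrt(1−rho): 1.20, 1.41 and 1.83 at rho 0.3, 0.5 and 0.7. The size is 2 × [1 − Φ(1.96 / sqrt(1−rho))] = 1.9%, 0.6% and 0.03%. The simulation gave 0.017, 0.007 and 0.000.

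That assumes units do not differ in mean change. If unit-level change has variance τ², a unit's mean change has true variance τ² + 2σ²(1−rho)/m, against about 2σ²/m in the model. With m = 432/28 = 15.4, the two errors cancel at about τ² = 2 × rho × σ²/m. At rho 0.5 this is 1.0/15.4 = 0.065σ², an SD between units of about 0.25σ. Below that the test is conservative; above it, anti-conservative.

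**What Table 7 implies.** Take z from the bootstrapped p-value, compute the power of a correctly sized test, and compare it with the power printed.
- EF on SES: boot.p .058 gives z = 1.57 and expected power 0.35; printed 0.38. This implies a null rejection rate of about 6%.
- TEC on second language: boot.p .436 gives z = 0.16 and expected power 0.053; printed 0.05. At rho 0.5 it would be about 0.11.
- Over the six distinct columns, the implied ratio of true SD to model standard error is 0.99 to 1.09, a null rejection rate of about 5% to 7%. Taking the SD instead from the beta intervals read literally as 5 to 95% gives about 5% to 11%.

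**The case against.** The strongest case against concerns size and reach.

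**Size.** A reader might infer that RQ5 tests reject true nulls two to three times too often. That needs rho between about 0.42 and 0.85. Such values are plausible for repeated ability tests, but the article gives no pre-post correlation, and at rho 0.2 to 0.3 the factor is 1.5 to 1.7. The only evidence in the article, Table 7, points lower: roughly 1.0 to 1.4 times from boot.p, and at most 2.2 times from the intervals. This stands as a limit on what can be claimed. It does not clear the model. Table 7 rests on pilot data whose pretest language scores were entirely interpolated, and its EF columns for Sex and 2nd lang. are identical in every row, so it says little about rho in the trial.

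**Reach.** A reader might also infer that 864 records are handled as independent children in every RQ5 analysis. They are not. Unit and preschool intercepts remain in the model; 864 is a ceiling for behavioural outcomes; selective attention has at most 246 records; and the communication rating has no pretest record to duplicate. In the hypothesis relating socioemotional skills to language, the predictor may vary by occasion, and the sqrt(1+rho) formula would then not apply. Table 1 also allows a correlation or t-test as an alternative for RQ5. These restrictions stand.

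**The missing terms may be implied.** RQ1 describes children nested in units as a general feature of mixed models, and the Discussion mentions random slopes at each level. Neither places a child effect in the RQ5 formula, and the slopes conflict with the intercept-only models. A unit-level slope on time would supply the unit-by-time term, so the two statements need reconciling.

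**Conflict with RQ1.** One might say that the Intervention × Time result will contradict RQ1. It could differ, but a baseline-adjusted posttest model and a repeated-measures model can differ even when both are correctly specified. The point is only that this test has the wrong standard error.

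**Conclusion.** The fault is in the model as written, and its direction is certain for any positive rho. For outcomes measured on both occasions, RQ5 tests of covariates constant within child are anti-conservative. The size is conditional: about 8.6% to 14.4% for assumed rho of 0.3 to 0.8, never above about 16.6%, under two-sided testing at 5% with two records for every child. Neither a fixed multiple nor a defect in every RQ5 hypothesis is supported by the article.

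The Intervention × Time test is conservative unless unit-level change variance is large relative to 2 × rho × σ²/m. The article gives no figure from which to judge that variance.

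This should be fixed before RQ5 is analysed. It is not critical to the trial's main conclusions, because RQ5 concerns background associations and the RQ1, RQ2 and RQ4 models take one record per child.

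**What to change.** 1. Add a random intercept for child, nested in unit and preschool, or an equivalent within-child covariance, to the RQ5 model for every outcome measured at both occasions. State how communication, rated at posttest only, will be analysed.
2. Either add a unit-by-time random effect so that Intervention × Time can be interpreted, or delete the sentence presenting this model as a further test of intervention effects.
3. Reconcile the RQ5 formula, which has intercepts only, with the Discussion's statement about random slopes.
4. Rerun Table 7 with the corrected model and check the duplicated EF columns.

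The cost is one or two variance terms and a rerun of the existing simulation. No new data are needed. RQ5 power, already at most 0.38 in Table 7, may come out somewhat lower.

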### RQ6 analyses: Background - background analyses

RQ6 hypotheses regarding relationships between background variables will be tested on the basis of the significance of Pearson or spearman correlation coefficients, depending on the types of variables at hand.

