### Hypotheses

On the basis of findings in earlier studies, we formulated seven sets of hypotheses corresponding to each of the seven research questions. The study aims to address the research questions by testing each of these hypotheses, listed in Table 1 below. For each hypothesis, Table 1 shows the outcome variable that is hypothesized to be affected, the intervention(s) or predictor either to affect or to be correlated with that outcome variable, the kind of effect or relationship that the hypothesis involves, for research questions 3 and 4, the mediating or moderating variables, the measure(s) used to estimate the outcome variable of the hypothesis at hand, and, finally, the kind of analysis method that will be conducted in order to test the hypothesis. In the following sections, we describe the method, the study design, the measurements and the analyses that will be used to test these hypotheses.

**Table 1 Tab1:** Hypotheses corresponding to each of the seven research questions described in terms of the affected outcome variable, the affecting intervention(s) or correlated predictor, the effect or relationship type, the mediating or moderating variable (if applicable), and analysis method used for hypothesis testing

Research question	Outcome variable(s)	Intervention/ Predictor	Effect	Mediator / moderator	Measure(s)	Analysis
RQ1: Intervention effects	EF	SEMLA & DIL	Positive intervention effects	–	Selective attention difference, EF indice difference	Mixed effects modelling
	Early Maths skills	SEMLA & DIL	Positive intervention effects	–	Maths difference	Mixed effects modelling
	Socioemotional skills	SEMLA & DIL	Positive intervention effects	–	TEC difference	Mixed effects modelling
	Communication	SEMLA & DIL	Positive intervention effects	–	Communication indice difference	Mixed effects modelling
	Language	SEMLA & DIL	Positive intervention effects	–	Language indice difference	Mixed effects modelling
RQ2: Intervention differences	Maths	SEMLA vs. DIL	Stronger effect of DIL	–	Maths difference	Planned comparisons
	EF	SEMLA vs. DIL	Differential effect	–	Selective attention difference, EF indice difference	Planned comparisons
	Communication	SEMLA vs. DIL	Stronger effect of SEMLA	–	Communication indice difference	Planned comparisons
	Language	SEMLA vs. DIL	Stronger effect of SEMLA	–	Language indice difference	Planned comparisons
RQ3: Mediating effects	Socioemotional skills	SEMLA & DIL	EF mediated effect	EF	TEC difference	Test of mediation effect

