	SECDI	Age	Positive relationship	–	SECDI	Correlation / mixed model
	Preschool start	Other L1	Higher mean for Swedish L2 children	–	Preschool start	t-test / mixed-model
	Preschool time	SES	Positive relationship	–	Preschool time	Correlation / mixed model
	SES	Multilingual	Higher mean for Swedish L1 children	–	SES	t-test / mixed-model
	SECDI	SES	Positive relationship	–	SECDI	Correlation / mixed model
RQ7: Intervention effect differences	EF	SEMLA vs. DIL	Less variation in DIL	–	Selective attention difference, EF indice difference	F-test of variance equality
	Early Maths skills	SEMLA vs. DIL	Less variation in DIL	–	Maths difference	F-test of variance equality
	Socioemotional skills	SEMLA vs. DIL	Less variation in DIL	–	TEC difference	F-test of variance equality
	Communication	SEMLA vs. DIL	Less variation in DIL	–	Communication indice difference	F-test of variance equality
	Language	SEMLA vs. DIL	Less variation in DIL	–	Language indice difference	F-test of variance equality

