### RQ1 analyses: Intervention effects

For RQ1 hypotheses, mixed effects modelling will be used to test the null hypotheses that there are no intervention effects on each of the respective outcome variables. Mixed effects modelling allows for the inclusion of multiple hierarchically nested random effects, such as children nested within preschool units and preschool units nested within preschools (e.g., [100]). The mixed effects model can thereby account for systematic influences of preschool units or preschools on the outcome variables. The model formula for the RQ1 hypothesis analyses is:

$$ {\mathrm{POSTSCORE}}_{\mathrm{ijk}}=\kern0.5em {\upalpha}_{0\mathrm{jk}}+{\upalpha}_{00\mathrm{k}}+{\upbeta}_1{\mathrm{INTERVENTION}}_{0\mathrm{jk}}+{\upbeta}_2{\mathrm{Y}}_{\mathrm{ijk}}+{\upbeta}_3{\mathrm{PRESCORE}}_{\mathrm{ijk}}+{\upbeta}_4{\mathrm{FIDELITY}}_{\mathrm{ijk}}+{\upbeta}_5{\mathrm{ECERS}}_{00\mathrm{k}}+{\upvarepsilon}_{\mathrm{ijk},}\ {\upvarepsilon}_{\mathrm{ijk}}\sim \mathrm{N}\left(0,{\upsigma^2}_{\upvarepsilon \mathrm{ijk}}\right),{\upalpha}_{\mathrm{j}}\sim \mathrm{N}\left(0,{\upsigma^2}_{\upalpha \mathrm{j}}\right),{\upalpha}_{\mathrm{k}}\sim \mathrm{N}\left(0,{\upsigma^2}_{\upalpha \mathrm{k}}\right) $$

In the models, the *i*th child is nested within the *j*th preschool unit, which in turn is nested within the *k*th preschool.

These models predict the postscore of the given outcome measure for child *i* as a function of the intervention administered at preschool unit *j*, using the control intervention as the baseline category. They also control for the set of background variables Y of child *i*, as well as the prescore measure of child *i*, centered around zero, as well as the fidelity score for child *i*, as explained in more detail above. Further, they control for the total ECERS rating of preschool *k*, thereby taking into account any influence of preschool quality on the outcome variables. Finally, they include individual intercepts α for each preschool *k*, as well as individual intercepts α for each preschool unit *j*, thereby controlling for systematic differences between preschool units and preschools with respect to the outcome variables.

Separate models will be conducted on selective attention, early maths skills and emotional comprehension, as well as on the composite measures of EF, language and communication.

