The weaknesses connected to the project concern implementation of the study across preschools. Different engagement levels have been noted from different practitioners, and although the control preschools were enrolled in a self-evaluative assessment (BRUK) in the hopes of making them feel that they were actively involved in the study, there is a possibility that being assigned to the control condition in and of itself creates a sense of alienation from the project that could affect the outcome. The major obstacle observed throughout the project was, however, the different levels of participation found in different preschools as a result of particular individuals being more or less personally engaged in the tasks. Although this is a problem for a controlled study, it reflects the everyday situation of all educational practices. In the future, ways to measure and handle the “human aspect” of pedagogical reality as an influential factor in its own right need to be addressed. Thorough qualitative analysis of the interaction data from the present project could, in its continuation, contribute to a deepened discussion and knowledge of how we handle this influential but evasive reality.

The analysis methods chosen are ideal for analysing data sets such as the present one. In particular, by using mixed effects modelling it is possible to account for the hierarchical structure of the data, with children nested within preschool units, and preschool units nested within preschools. By including random slopes for each of these levels, the mixed effects models account for systematic variation that might exist between preschools or preschool units. The mixed effects model also allows for the inclusion of independent variables and covariates at different levels of nesting, such as the inclusion of interventions and the ECERS-3 scores on the preschool unit level, together with other covariates at the child level.

The results of the study are limited, containing outcomes from only 432 children of the approximately 500,000 attending Swedish preschools. However, the results carry the seed for a preschool setting based on evidence from a multifaceted investigation including considerations of children’s development through both measurable, quantitative test-scores on general abilities, and fine-grained qualitative analyses of skills not necessarily visible except through in-depth analyses of interactions between children and pedagogues.

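### RQ6: the analysis section keeps only child-level correlations and drops the mixed model that Table 1 lists, so nesting in preschools is ignored and true nulls can be rejected too often

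*Protocol article*

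**What the plan says.** The Hypotheses section presents Table 1 as showing, for each hypothesis, "the kind of analysis method that will be conducted in order to test the hypothesis". Of the six RQ6 rows, four read "Correlation / mixed model": preschool time on preschool start, SECDI on age, preschool time on SES, and SECDI on SES. The other two read "t-test / mixed-model": preschool start by other first language, and SES by multilingual status. Table 1 does not say which side of the slash applies.

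The section headed RQ6 analyses is a single sentence. It says that these hypotheses "will be tested on the basis of the significance of Pearson or spearman correlation coefficients, depending on the types of variables at hand". It names no mixed model and no cluster term.

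On the structure of the data, the Sample characteristics section states: "The sample consists of 432 children from 28 preschool units, which, in turn come from 18 preschools". The RQ1 section gives the reason for the modelling approach: "The mixed effects model can thereby account for systematic influences of preschool units or preschools on the outcome variables". The Discussion repeats it: "by using mixed effects modelling it is possible to account for the hierarchical structure of the data, with children nested within preschool units". The RQ5 rows of Table 1 use the same slash notation as the RQ6 rows, and the RQ5 section settles it in favour of mixed models with an intercept for each preschool and each unit.

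**The concern.** Two places in the protocol give the test for the same six hypotheses, and they do not give the same rule. Table 1 leaves a choice open. The RQ6 section closes it by removing the option that accounts for nesting, and gives no reason.

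The significance test of an ordinary Pearson or Spearman coefficient treats the 432 children as independent. SES, language background, weekly preschool hours and age at preschool start may well differ between preschools. When both variables in a pair do so, chance differences between a few preschools can look like a relationship between children, and the child-level p-value is too small. At stake is whether a reported relationship among background variables can be taken at its nominal 5% level. The p-value correction planned in the protocol covers RQ1 to RQ4, so it does not change the RQ6 p-values.

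**Working it through.** **Passages side by side**

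| Place | Rule for relationships with background variables |
|---|---|
| Table 1, RQ5 rows | correlation or t-test, or mixed model |
| RQ5 section | mixed model, unit and preschool intercepts |
| Table 1, RQ6 rows | correlation (4 rows) or t-test (2 rows), or mixed model |
| RQ6 section | Pearson or Spearman only |

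The real difference is mixed model against none. For the two group comparisons, Pearson's coefficient with a binary variable is the equal-variance t-test; a numerical check gave the same p-value (0.0405) for both. The absence of a t-test from the RQ6 section is therefore no defect.

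**Size of the effect**

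The protocol states no error rate, power or ICC for RQ6, so there is no figure to reproduce.

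Inputs from the protocol: 432 children, 28 units, 18 preschools, alpha 0.05 (Power calculations section). Assumptions: two-sided tests; 10 preschools with two units and 8 with one (10 × 2 + 8 = 28); 12 units of 16 children and 16 of 15 (192 + 240 = 432); ICCs of 0 to 0.3 for each variable.

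Size-weighted mean cluster size, m = Σn² / Σn:
- Units: (12 × 16² + 16 × 15²) / 432 = 6672 / 432 = 15.4.
- Preschools (6 of 32, 4 of 30, 8 of 15 children): (6 × 32² + 4 × 30² + 8 × 15²) / 432 = 11544 / 432 = 26.7.

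Approximate design effect for a correlation under the null: DE = 1 + (m − 1) × ICCx × ICCy. Actual type I error = 2 × [1 − Φ(1.96 / √DE)].

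- Either ICC 0: DE = 1, type I error 5.0%.
- Unit level, 0.1/0.1: DE = 1 + 14.4 × 0.01 = 1.144; 1.96 / √1.144 = 1.832; 6.7%.
- Unit level, 0.2/0.2: DE = 1 + 14.4 × 0.04 = 1.576; 1.561; 11.8%.
- Preschool level, 0.1/0.1: DE = 1 + 25.7 × 0.01 = 1.257; 1.748; 8.0%.
- Preschool level, 0.2/0.2: DE = 1 + 25.7 × 0.04 = 2.028; 1.376; 16.9%.

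Simulation of Pearson's test under a true null with this structure (20,000 runs per setting):

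| ICCs | Clustering at unit level | Clustering at preschool level |
|---|---|---|
| either 0 | 5.0% | 5.0% |
| 0.05 / 0.05 | 5.2% | 5.8% |
| 0.1 / 0.1 | 6.7% | 7.5% |
| 0.1 / 0.2 | 8.3% | 11.0% |
| 0.2 / 0.2 | 11.5% | 15.9% |
| 0.3 / 0.3 | 19.3% | 27.4% |

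Formula and simulation agree closely. At preschool level with ICCs 0.2/0.2, Spearman gave 15.4% (4,000 runs). A binary predictor with 20% prevalence, its ICC set on the underlying scale, gave 10.7%.

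**After the change**

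A mixed model with a preschool intercept (400 runs per setting, Monte Carlo error about 1 to 2 percentage points, some convergence warnings) rejected 4.5%, 5.5% and 2.5% of true nulls at ICCs 0/0.2, 0.1/0.1 and 0.2/0.2. Pearson on the same data gave 4.3%, 9.0% and 14.5%. A separate run with 18 equal preschools of 24 children (500 replicates per setting) gave 5.2% for the mixed model at both 0.1/0.1 and 0.2/0.2, against 8.8% and 15.8% for Pearson. The excess disappears.

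**The case against.** The best defence is that nothing is contradicted. In four of the six rows Table 1 itself offers a correlation, and the RQ6 section simply picks it. In the other two, Pearson with a binary variable is the equal-variance t-test that Table 1 offers. This stands as far as it goes: the section narrows a choice, and under Pearson it departs from Table 1 only on the mixed-model side. It does not explain why the cluster-aware option was dropped here when the same notation was settled the other way for RQ5.

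A reader might infer that RQ6 nulls will be rejected too often as a matter of course. The documents do not support that. Inflation needs both variables in a pair to cluster, and no ICC is given. For SECDI on age, for example, age may hardly differ between preschools, and the plain test would then be close to its nominal level. At ICCs of 0.05 the excess is below one percentage point.

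A reader might also infer that the trial's main results are at risk. They are not: RQ6 concerns relations among background variables, the design is described as partly exploratory, and no intervention contrast or power figure rests on RQ6. Leaving RQ6 outside the p-value correction is a declared choice and no defect in itself.

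Finally, RQ6 is not the only part without a cluster term. The mediation regressions for RQ3 and the variance tests for RQ7 name none either. That is true, but it is no reason to leave RQ6 as it is.

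**Conclusion.** The point holds in a limited form. Table 1 and the RQ6 section do not state one rule, and the rule in the section omits the only listed method that reflects children nested in units and preschools, a structure that the protocol says its mixed models are there to handle. Followed as written, the tests can be anti-conservative.

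How far cannot be fixed from the documents. Over assumed ICCs of 0 to 0.3 the true rate at a nominal 5% runs from about 5% to about 27%. The moderate cases are 6.7% to 7.5% at 0.1/0.1 and 11.5% to 15.9% at 0.2/0.2, the lower figure for clustering at unit level and the higher at preschool level. These rates also rest on an assumed split of units among preschools and on normally distributed variables, apart from the separate binary-predictor check. Only statements about background relationships are affected. The correction is worth making because it is cheap, not because the trial's main conclusions depend on it.

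**What to change.** State one rule in the RQ6 section and in the six RQ6 rows of Table 1: regress one background variable on the other in a mixed model with random intercepts for unit and preschool, for continuous and group predictors alike. Where the response is ordinal or skewed, as the coarse SES score may be, allow a cluster-robust equivalent, for example on ranks. Report Pearson and Spearman coefficients as descriptive only, and delete the correlation and t-test alternatives from those rows.

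While editing, align the wording of the sixth research question. The Research questions list describes it as relations among outcome variables, whereas Table 1 and the RQ6 section treat it as relations among background variables.

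The cost is one or two sentences and six table cells. No new data are needed, and the model type is already planned for RQ5. The downside is slightly larger p-values for some pairs.
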